## Abstract

**Abstract:**

The main aim of this study is to compare the use of non-invasive ventilation (NIV) via helmet versus face mask where different interfaces and masks can apply NIV. However, some of the limitations of the NIV face mask were air leak, face mask intolerance, and requirement of high positive end expiratory pressure, which could be resolved with the use of the helmet NIV. NIV facemask will be applied as per the facial contour of the patient. NIV helmet is a transparent hood and size will be measured as per the head size. Both groups will have a standard protocol for titration of NIV.

Patients aged more than 18 years old and diagnosed with acute respiratory distress syndrome as per Berlin definition will be enrolled in the study after signing the informed consent. Subjects who met the inclusion criteria will receive 1 of the 2 interventions; blood gases, oxygenation status [Po2/Fio2] will be monitored in both groups. The time of intubation will be the main comparison factor among the 2 groups. The primary and secondary outcomes will be measured by the number of patients requiring endotracheal intubation after application of helmet device, Improvement of oxygenation defined as PaO2/FiO2 ≥ 200 or increase from baseline by 100, duration of mechanical ventilation via an endotracheal tube, intensive care unit length of stay, death from any cause during hospitalization at the time of enrolment, need for proning during the hospital stay, intensive care unit mortality, and the degree to which overt adverse effects of a drug can be tolerated by a patient including feeding tolerance.

**Trial registration number::**

NCT04507802.

**Protocol version::**

May 2020

## Introduction

1

Pneumonia is one of the leading causes of intensive care unit (ICU) admissions. Among pneumonia patients, acute respiratory distress syndrome (ARDS) is the most common etiological factor leading to respiratory failure. Since March 2020, worldwide ICU admissions were mainly ARDS patients infected with coronavirus disease (COVID-19).

Within intensive care units, approximately 10% to 15% of admitted patients, and up to 20% of mechanically ventilated patients meet ARDS criteria.^[1–3]^

In Qatar, between February 28 and April 18, 2020, 5685 cases of COVID-19 were identified. More than 90% were with minimal symptoms or asymptomatic, with 2.0% required critical care support.^[4]^ COVID-19 patients with existing comorbidities (mainly hypertensive and diabetes) had higher C-reactive protein (CRP) levels (inflammatory response), a higher ICU admission rate, extended hospitalization, and more oxygen use.^[5,6]^ On the other hand, patients with eosinophilia had a lower level of CRP, milder clinical course and better disease outcomes compared to those without eosinophilia.^[7]^

The Berlin definition of ARDS requires that all the following criteria be present for diagnosis.^[8,9]^

1.Respiratory symptoms must have begun within 1 week of a known clinical insult, or the patient must have new or worsening symptoms during the past week.2.Bilateral opacities must be present on a chest radiograph or computed tomographic (CT) scan. These opacities must not be fully explained by pleural effusions, lobar collapse, lung collapse, or pulmonary nodules.3.The patient's respiratory failure must not be fully explained by cardiac failure or fluid overload. An objective assessment (echocardiography) to exclude hydrostatic pulmonary edema is required if no risk factors for ARDS are present.4.A moderate to severe impairment of oxygenation must be present, as defined by the ratio of arterial oxygen tension to the fraction of inspired oxygen (PaO_2_/FiO_2_). The severity of the hypoxemia defines the severity of the ARDS:Mild ARDS – The PaO_2_/FiO_2_ is >200 mm Hg, but ≤300 mm Hg, on ventilator settings that include positive end-expiratory pressure (PEEP) or continuous positive airway pressure (CPAP) ≥5 cm H_2_O.Moderate ARDS – The PaO_2_/FiO_2_ is >100 mm Hg, but ≤200 mm Hg, on ventilator settings that include PEEP ≥5 cm H_2_O.Severe ARDS – The PaO_2_/FiO_2_ is ≤100 mm Hg on ventilator settings that include PEEP ≥5 cm H_2_O

Acute respiratory distress syndrome (ARDS) is characterized by a progressive form of respiratory failure with hypoxia, bilateral lung infiltrates on chest imaging, and onset within a week of the triggering event. There are many common etiological factors for ARDS which can be classified into direct and indirect lung injury factors. The commonest direct lung injury cause is pneumonia which includes both bacterial and viral.

The pathology of ARDS lung evolves through 3 phases with inflammatory changes. The inflammation leads to increased microvascular permeability which leads to extravascular fluid accumulation. There will be interstitial and alveolar edema which progresses to fibrosis. The characteristic lesion termed diffuse alveolar damage, undergoes progression from an exudative to proliferative, to a fibrotic phase. Histologic studies in ARDS have demonstrated a pattern of diffuse pulmonary endothelial injury associated with both macro and microscopic thrombi formation. These early changes progress to fibro cellular intimal proliferation that can obliterate small vessels.^[10]^

The treatment of ARDS is a field where there are lots of researches being done. Until now, the treatment modalities that have shown mortality benefit in ARDS are neuromuscular blockade, prone ventilation and extracorporeal membrane oxygenation. There are few recent studies in ARDS treatment using NIV to avoid endotracheal intubation and mechanical ventilation-induced adverse events. The main side effects associated with mechanical ventilation include the need for sedation and paralysis, barotrauma, critical illness polyneuropathy. The non-invasive mechanical ventilation (NIV) is any form of administration of positive pressure using an interface or a face mask, without the need of using an endotracheal tube.^[11]^

Hypoxemic acute respiratory failure is the most common form of acute respiratory failure associated with ARDS. The application of positive pressure in hypoxemic acute respiratory failure produces decreased intrapulmonary shunt and thereby improves oxygenation. This occurs by the recruitment of collapsed alveoli, prevents collapse previously opened by the positive pressure, increases FRC, and improves the balance of the ventilation-perfusion mismatch.^[12,13]^

There are also some studies which showed benefit with the use of NIV in community-acquired pneumonia patients.^[8,14]^

NIV can be applied by different interfaces and masks. The limitations of the face mask NIV that are found in some studies were air leak, face mask intolerance, and requirement of high PEEP.^[15–17]^

These obstacles were overcome to some extent by the introduction of helmet NIV. It provided better patient tolerance, less air leak as there is no contact with the facial tissues, and a better seal at the neck level. To our knowledge, there is only 1 randomized trial that compared the effects of helmet NIV versus face mask NIV in preventing endotracheal intubation.^[18]^ The results of the trial showed the intubation rate was 61.5% (n = 24) for the face mask group and 18.2% (n = 8) for the helmet group (absolute difference, –43.3%; 95% CI, –62.4% to –24.3%; *P* < .001). As evidenced from the mentioned trial, we hypothesize the use of an NIV helmet can reduce intubation in ARDS caused by pneumonia, including COVID-19.

## Objectives

2

Primary objective: To assess the efficacy of non-invasive ventilation with HELMET in reducing endotracheal intubation rates in comparison with NIV face mask among patients with ARDS.

Secondary objective: to explore any improvement in oxygenation, time to intubation, ventilation days, and tolerance to HELMET NIV in comparison with facemask NIV.

## Trial design

3

This is a phase-III, randomized, comparative, parallel assignment, open-label clinical study

## Methods: participants, interventions, and outcomes

4

### Study setting

4.1

The study will take place in the intensive care unit in Hazm Mebaireek General Hospital in Qatar. All included patients are diagnosed with ARDS, type 1, or type 2 respiratory failure, and they are conscious and alert. All the investigators on this protocol are from Hazm Mebaireek General Hospital. The details of the procedure and interventions are mentioned below in the background and methods sections.

### Eligibility criteria

4.2

1.Patients with ARDS as per Berlin definition2.Age: 18 years and above

### Exclusion criteria

4.3

1.Patients with altered sensorium [Glasgow Coma Scale less than 13]2.Pregnant patients3.Hemodynamic instability4.Morbidly obese5.Patients with tracheostomy6.Severe acidosis [PH less than 7.15]7.Patients with glaucoma8.Patients with a history of vertigo

### Outcomes measures

4.4

Primary outcome measure:

1.Need for endotracheal intubation [ time frame: 6 weeks].Number of patients requiring endotracheal intubation after application of helmet device

Secondary outcome measures:

1.Improvement in oxygen saturation [time frame: 2 weeks]Improvement of oxygenation defined as “PaO2/FiO2 ≥ 200 or increase from baseline by 100”.2.Ventilator-free days [time frame: 28 days]Duration of mechanical ventilation via endotracheal tube.3.Intensive care unit length of stay [time frame: 4 weeks]The number of days admitted to the intensive care unit.4.Overall mortality [time frame: 90 days]Death from any cause during hospitalization at the time of enrollment.5.Need for proning [time frame: up to 24 weeks]Need for proning during the hospital stay.6.ICU mortality [time frame: 28 days]Death from any cause during ICU hospitalization at the time of enrollment.7.Patient tolerability [time frame: 28 days from randomization]The degree to which overt adverse effects of a drug can be tolerated by a patient, including feeding tolerance.

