### Type and classification of study- randomized control trial

5.1

*Intervention* – application of NIV by HELMET after randomizing the selected patients with odd and even numbers.

*Control group-* application of NIV with face mask after randomizing the selected patients with ARDS caused by COVID-19 and other pneumonia, type 1 and type 2 respiratory failure, Conscious and alert patients. NIV facemask will be applied as per the facial contour of the patient. NIV helmet is a transparent hood and size will be measured as per the head size. Both groups will have a standard protocol for titration if NIV. First, PEEP will be increased gradually to target spo2 above 90% with a Fio2 of 60% or less. Pressure support or IPAP will be increased slowly by 2 to 3 cm H2O to target a respiratory rate less than 30/min. The patient will be connected to non-invasive ventilation for 4 hours and will be on a high-flow nasal cannula for 1 hour. This 4:1 ratio will be continued till his condition improves or he will get intubated if he is worsening on non-invasive ventilation. Blood gases, oxygenation status [Po2/Fio2] will be monitored in both groups. The time of intubation will be the main comparison factor among the 2 groups. The intubation criteria will be the same for 2 groups which include, Worsening P/F ratio worsening acidosis, hemodynamic instability, poor neurological status.

The decision for intubation will be decided by the primary physician on duty

The intubated patient will be ventilated with lung-protective ventilation as per ARDS protocol.

If a patient in the control group is not tolerating the mask, they will be given the helmet in the other group as rescue therapy.

The weaning criteria will be the same for both groups and patients will be weaned to a high-flow nasal cannula or non-rebreathing mask. For weaning, pressure support and PEEP will be reduced gradually and will be discontinued if the respiratory rate is less than 30/min and P/F ratio more than 150 with a PEEP of 5 cm H20. If 1 patient is out of NIV for more than 12 hours a day for 48 hours, that will be considered as weaning.

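### The primary outcome counts intubations only, so a death without intubation adds no event; add the composite with death as primary or as a pre-specified key sensitivity analysis

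*Protocol article*

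**What the plan says.** The Outcomes measures section of the protocol article gives the primary outcome as "Need for endotracheal intubation [ time frame: 6 weeks" and describes it as "Number of patients requiring endotracheal intubation after application of helmet device". I read it as applying to both arms, since the Objectives section sets the aim as "To assess the efficacy of non-invasive ventilation with HELMET in reducing endotracheal intubation rates" in comparison with the face mask. Fewer intubations is therefore the stated benefit.

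Death appears only among the secondary outcomes: overall mortality (90-day frame, defined as "Death from any cause during hospitalization at the time of enrollment") and ICU mortality (28-day frame). No section says how a patient who dies without intubation enters the primary count.

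The section on type and classification of study adds "The time of intubation will be the main comparison factor among the 2 groups", again without a rule for death. It gives the same intubation criteria for both arms, without numerical thresholds, and states "The decision for intubation will be decided by the primary physician on duty". The Trial design section describes a "randomized, comparative, parallel assignment, open-label clinical study".

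**The concern.** Death before intubation prevents the primary event from occurring. If only intubations are counted, that patient contributes a zero, as does a patient who improves and is weaned from NIV. An arm with more un-intubated deaths then shows a lower primary event rate for a reason that is not benefit.

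Such deaths are possible in this trial. Eligibility is ARDS by the Berlin definition, which the Introduction sets out to include severe disease. None of the eight exclusions concerns a limit on intubation. The physician on duty decides on intubation knowing the assigned interface, so whether and when a failing patient is intubated could differ between arms.

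At stake is the reading of the primary comparison in a trial of 60 patients, where single events carry weight.

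**Working it through.** The point concerns a definition, so the plan has no figure to reproduce. The arithmetic only shows how sensitive the comparison is.

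**Inputs**
- Total sample size 60 (Sample Size & Recruitment). No allocation ratio is stated; 30 per arm is my assumption.
- Rate of un-intubated death: not in the documents. Every count below is hypothetical, and each case puts all such deaths in one arm, which is the worst case.
- Test: two-sided Fisher exact test on intubated versus not intubated, unless stated otherwise. The article names no test.

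**Step 1: weight of one death.** 1/30 = 3.3 percentage points.

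**Step 2: equal true failure, one-sided deaths.** Let failure mean intubation or death without intubation, with *f* failures in each arm, *k* of them un-intubated deaths in one arm and none in the other. The outcome as written compares *f* with *f* − *k*, an apparent difference of *k*/30. The true difference is 0.

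| *f* per arm | *k* in one arm | Reads as | Apparent difference | Fisher p |
|---|---|---|---|---|
| 12 (40.0%) | 4 | 12 vs 8 | 13.3 points | 0.41 |
| 12 | 7 | 12 vs 5 | 23.3 points | 0.084 |
| 12 | 8 | 12 vs 4 | 26.7 points | 0.039 |
| 18 (60.0%) | 3 | 18 vs 15 | 10.0 points | 0.60 |
| 18 | 6 | 18 vs 12 | 20.0 points | 0.20 |
| 18 | 8 | 18 vs 10 | 26.7 points | 0.069 |
| 18 | 9 | 18 vs 9 | 30.0 points | 0.037 |

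A handful of such deaths shifts the estimate. A false significant result needs 8 or 9, all in one arm.

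**Step 3: the same as probabilities.** With true failure of 50% in both arms and a share *d* of one arm dying un-intubated, the comparison as written is 50% against 50% − *d*. The normal-approximation chance of a two-sided 5% result favouring that arm is:
- *d* = 5%: 6%
- *d* = 10%: 12%
- *d* = 20%: 35%
- *d* = 30%: 69%

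**Step 4: hiding a real difference.** Take true failures of 18/30 and 8/30: 33.3 points, p=0.018. If 2 of the 18 are un-intubated deaths, the outcome reads 16 vs 8: 26.7 points, p=0.064. Two deaths are enough to lose significance in this example.

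**Step 5: do the secondaries repair it?** Their windows are 90 and 28 days against 6 weeks (42 days) for the primary, and neither separates deaths before intubation from deaths after it. They would show an imbalance in deaths but leave the primary count as it is.

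**The case against.** Several objections have force.

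- **No stated rule.** A reader might infer that the protocol scores an un-intubated death as a success. It does not say so; the zero is a consequence of counting intubations. The words on need and requirement could also be stretched to cover a patient who met the criteria and died first. No text says that, the objective speaks of intubation rates, and the reading would still miss deaths that never met the criteria.
- **Analysis-plan content.** Competing-event methods and sensitivity analyses are commonly left to a document not shown here, so their absence is not in itself a fault. What the event consists of, however, is fixed in this article as intubation alone.
- **Intubation is a legitimate endpoint.** It matches the objective and the intubation rates reported from the earlier trial in the Introduction. This stands, and it is why replacing the primary outright is more debatable than adding the composite.
- **Few such deaths may occur.** Worsening patients are to be intubated under common criteria, and unstable patients are excluded. This may keep the number low, but no figure is given. That intubation will be declined or withheld for some patients is likewise only a possibility left open by the exclusion list.
- **Size.** A reader might infer that a few deaths could create a positive trial. Step 2 does not support that, and balanced deaths would leave little or no bias in the difference.

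**Conclusion.** The point holds in a limited form. Applied exactly as written, the primary outcome gives no event to a patient who dies un-intubated, and the mortality secondaries do not correct this. The size and direction of any bias are unknown: the documents give no rate of such deaths and no reason to expect more of them under one interface than the other. It cannot be said that the plan favours either arm.

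Under the assumptions of 30 per arm and deaths confined to one arm, a few deaths distort the estimate, two can remove significance from a real difference, and about 8 to 9 are needed to produce significance from none. This is a cheap improvement to the outcome definition, not a defect that invalidates the trial.

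**What to change.** Either of two changes would do:

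1. Define the primary event as endotracheal intubation, or death without intubation, within 6 weeks of randomisation, and report both components by arm.
2. Keep intubation alone as primary and pre-specify that composite as the key sensitivity analysis. Report it beside the primary result, and require the two to agree in direction before benefit is claimed.

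Under either option, treat death as a competing event in the time-to-intubation comparison.

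The cost is one outcome sentence and one line of analysis. In-hospital deaths are already collected for the mortality secondaries; the sentence should also say whether a death after discharge but within 6 weeks counts. The downside is that deaths unrelated to the interface slightly dilute the contrast. Nothing in patient management changes.

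### The oxygenation outcome is not limited to the period before intubation, so a patient who failed NIV can be scored as improved on the invasive ventilator

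*Protocol article*

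**What the plan says.** Section 4.4 of the Protocol article lists, as the first secondary outcome, "Improvement in oxygen saturation [time frame: 2 weeks" and gives the responder rule "PaO2/FiO2 ≥ 200 or increase from baseline by 100". The abstract repeats the rule. Neither place adds a condition on the type of support, or on whether the value comes before or after intubation.

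Section 2 states what the secondary outcomes are for: "to explore any improvement in oxygenation, time to intubation, ventilation days, and tolerance to HELMET NIV in comparison with facemask NIV".

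Section 5.1 describes measurement and the course after failure. On measurement: "Blood gases, oxygenation status [Po2/Fio2] will be monitored in both groups", with no stated end at intubation. On failure: "he will get intubated if he is worsening on non-invasive ventilation", and then "The intubated patient will be ventilated with lung-protective ventilation as per ARDS protocol". The same section lets mask patients who do not tolerate the mask receive the helmet as rescue, and describes weaning to high-flow oxygen or a non-rebreathing mask.

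The Introduction cites one earlier randomised trial in which "the intubation rate was 61.5% (n = 24) for the face mask group and 18.2% (n = 8) for the helmet group".

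**The concern.** The objective compares two NIV interfaces. Once a patient is intubated, PaO2/FiO2 reflects the invasive ventilator and no longer either interface. A patient intubated because the ratio was worsening, who later reaches the threshold under invasive ventilation inside the 2-week window, satisfies the definition in the same way as a patient who improved on the helmet or mask.

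The two arms would not be affected equally. If the mask arm has more intubations, as the trial hypothesises, more of its patients can be credited with improvement after their interface has failed. The arm that fails more often gains more from the open definition, and a real advantage of the helmet on oxygenation would be understated.

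**Working it through.** **Reading the passages together.** The responder rule in section 4.4 sets a threshold and a window only. Section 5.1 supplies the route by which a failed patient goes on to invasive ventilation, and puts no end to P/F monitoring there. Nothing in the article removes a post-intubation value from the outcome. This is so whether the 2-week time frame means any value within 2 weeks or a single assessment at 2 weeks.

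**Plan's own figure.** The article gives no expected response rate for this outcome, so there is none to reproduce. The cited intubation gap does reproduce: 61.5% − 18.2% = 43.3 points.

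**Inputs**
- Intubation: mask 0.615, helmet 0.182 (Introduction, from the cited trial). Assumed to apply here and to fall within 2 weeks. The trial's own intubation outcome runs longer: "Need for endotracheal intubation [ time frame: 6 weeks".
- r: response in never-intubated patients, assumed 0.80 in both arms.
- q: share of intubated patients scored as improved on a value obtained after intubation, assumed equal in both arms and varied. Responses before intubation are ignored in this simple model.

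**Formula.** Proportion scored improved = (1 − intubation rate) × r + intubation rate × q.
- Mask: 0.385 × 0.80 + 0.615q = 0.308 + 0.615q
- Helmet: 0.818 × 0.80 + 0.182q = 0.654 + 0.182q
- Helmet minus mask: 0.433 × (0.80 − q)

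| q | Mask | Helmet | Difference (points) |
|---|---|---|---|
| 0 | 30.8% | 65.4% | 34.6 |
| 0.25 | 46.2% | 70.0% | 23.8 |
| 0.50 | 61.6% | 74.5% | 13.0 |
| 0.75 | 76.9% | 79.1% | 2.2 |

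The difference is zero at q = 0.80 and negative only above it (at q = 0.90, 0.433 × (−0.10) = −4.3 points).

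**Sensitivity to r.** With r = 0.60 the difference is 26.0 points at q = 0 and 4.3 at q = 0.50. With r = 1.00 it is 43.3 and 21.7. The amount lost is 0.433 × q whatever r is.

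**Unequal q.** If q differs by arm, the contribution of post-intubation responses is 0.182 × q(helmet) − 0.615 × q(mask). This is negative, and so dilutes a helmet benefit, unless q(helmet) exceeds 0.615/0.182 = 3.4 times q(mask).

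**In patients.** With an assumed 30 per arm (the article gives only 60 in total) and q = 0.50, the failures scored as improved number 30 × 0.615 × 0.50 = 9.2 in the mask arm and 30 × 0.182 × 0.50 = 2.7 in the helmet arm.

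**The case against.** The strongest reply is that the article is silent and does not include post-intubation values. The objective speaks of NIV, and the monitoring sentence sits within the NIV text of section 5.1, so a P/F value on NIV may be what was meant. The scoring of intubated patients could also be fixed in a fuller document. It stands that a reader might infer the plan deliberately counts ventilator values, and the document does not support that. But the threshold and window are stated, and followed literally they admit such values. The point concerns a stated rule, not only an absent detail.

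The illustration has limits, and these also stand. With r equal in both arms, the 35 points at q = 0 are the cited intubation gap multiplied by 0.80. They restate the primary contrast and are not separate evidence about oxygenation. That figure also scores every intubated patient as a non-responder, so it does not estimate the amended outcome, which credits a response reached before intubation.

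A reader might go further and infer that the contrast would reverse. With equal r and q in the two arms, that needs q above 0.80, meaning failed patients respond more often than those who never failed. Nothing in the article suggests this.

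Comparing oxygenation by randomised arm regardless of intubation is a legitimate treatment-policy question if it is declared. It does not isolate the effect of the interfaces that section 2 names.

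**Conclusion.** The point holds in a limited form. As written, secondary outcome 1 can score a patient who failed NIV as improved, and this tends to dilute the helmet-versus-mask contrast if intubation is more frequent with the mask. The direction rests on that higher intubation rate and on some intubated patients reaching the threshold only after intubation. The size is not known: 35, 24, 13 and 2 points at q = 0, 0.25, 0.50 and 0.75 is a range under assumed r and q and borrowed intubation rates.

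The definition should be amended, but the consequence is bounded. The outcome is one of seven secondary outcomes under an objective worded as exploratory, and the primary outcome is untouched. A reader might take it, as the first listed, to be the trial's main mechanistic outcome; the document does not give it that status. The heading names saturation while the definition uses PaO2/FiO2, which is an editorial slip only.

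**What to change.** Amend the definition in section 4.4 as follows:
- Improvement means that the PaO2/FiO2 criterion is reached within 2 weeks, before any intubation, while the patient is on non-invasive support of any kind: NIV, the high-flow interval, or after weaning.
- Intubation or death before that point counts as not improved.
- Analysis is by randomised arm, so mask patients given the rescue helmet stay in the mask group.
- The result regardless of intubation is reported as a sensitivity analysis.

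The definition should not require the assigned interface. Section 5.1 allows NIV to be stopped at a P/F ratio above 150, so a weaned patient who passes 200 later would be lost. Responses after mask-to-helmet rescue would also be dropped in one arm only. Nor should it rely on a next scheduled blood gas, because the article gives no schedule.

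The outcome heading should be changed from saturation to PaO2/FiO2.

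The cost is a short change of wording. Blood gases are already monitored, and section 5.1 already makes the time of intubation a comparison factor, so no new type of data is needed. The downside is a lower responder rate in both arms and partial overlap with the primary outcome, since intubation before response now counts against the patient in both.

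### Patients with mild ARDS already meet the oxygenation-improvement threshold at enrolment, so they count as improved without improving unless their assessed PaO2/FiO2 falls below 200

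*Protocol article*

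**What the plan says.** - **Outcome** (Protocol article, section 4.4 Outcomes measures, secondary outcome 1). The item is headed "Improvement in oxygen saturation [time frame: 2 weeks", and improvement is defined as "PaO2/FiO2 ≥ 200 or increase from baseline by 100". The two alternatives are joined by *or*, so either is enough. No condition is placed on the baseline value.
- **Eligibility** (section 4.2). The only clinical entry criterion is "Patients with ARDS as per Berlin definition", with no grade or upper PaO2/FiO2 limit.
- **Berlin definition as the protocol gives it** (section 1, Introduction). For mild ARDS the ratio "is >200 mm Hg, but ≤300 mm Hg". For moderate ARDS it "is >100 mm Hg, but ≤200 mm Hg, on ventilator settings that include PEEP" of at least 5 cm H2O. Severe ARDS is 100 or below. The lead-in to these grades reads "A moderate to severe impairment of oxygenation must be present".
- **Exclusions** (section 4.3). There are eight items. One concerns blood gases, "Severe acidosis [PH less than 7.15", and none concerns PaO2/FiO2 or ARDS grade.

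**The concern.** A responder outcome should be something a patient can reach only by responding. Here one eligible severity class is above the threshold before any NIV is applied. For those patients the outcome records that they entered with mild disease and did not drop below 200. It does not record that oxygenation improved.

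Two consequences follow for the comparison of helmet with mask. Patients who count as successes in either arm add the same amount to both rates and shrink any real difference. And because success depends on entry grade, an arm that happens to receive more mild patients will show a higher improvement rate even if the interface makes no difference. With 60 patients in total, a chance imbalance of that kind is plausible. Improvement in oxygenation is the first item in the secondary objective (section 2) and is repeated in the abstract, so the result is likely to be read as evidence about the helmet.

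**Working it through.** The protocol states no rate, sample size or power for this outcome, so there is no figure of its own to reproduce. The check has three parts.

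**1. Applying the rule to each grade**

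Let b be baseline PaO2/FiO2 and f the assessed value. The rule is: improved if f ≥ 200 or f − b ≥ 100. With no change (f = b), using integer baselines:

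| Grade (Introduction) | Baselines tried | Counted as improved |
|---|---|---|
| Mild | 201 to 300 | 100 of 100 |
| Moderate | 101 to 200 | 1 of 100 (only b = 200) |
| Severe | 50 to 100 | 0 of 51 |

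With a fall from a mild baseline:

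| b to f | Change | f ≥ 200? | Rise ≥ 100? | Improved? |
|---|---|---|---|---|
| 300 to 200 | −100 | yes | no | yes |
| 250 to 200 | −50 | yes | no | yes |
| 205 to 200 | −5 | yes | no | yes |
| 250 to 190 | −60 | no | no | no |
| 300 to 190 | −110 | no | no | no |

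So a mild patient counts as improved without improving, and can lose up to 100 and still count, but not if the assessed value is below 200.

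**2. Dilution of a true difference**

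Assumptions, none of them in the documents: 30 patients per arm (an equal split of the 60 in section 4.6); true response r of 30% with mask and 60% with helmet in non-mild patients; the same mild share m in both arms; every mild patient scored as improved.

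Observed rate = m + (1 − m) × r, so the observed difference = (1 − m) × 30 points. Power is by exact enumeration of both binomials, with a two-sided chi-square test at 0.05.

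| Mild share m | Mask | Helmet | Difference (points) | Power |
|---|---|---|---|---|
| 0% | 30% | 60% | 30 | 66% |
| 10% | 37% | 64% | 27 | 57% |
| 20% | 44% | 68% | 24 | 47% |
| One third | 53% | 73% | 20 | 36% |
| 50% | 65% | 80% | 15 | 25% |

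For example, at one third mild: mask 0.333 + 0.667 × 0.30 = 0.533; helmet 0.333 + 0.667 × 0.60 = 0.733.

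**3. Spurious difference from imbalance**

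Suppose the interface has no effect, and 30% of non-mild patients respond in both arms. If the mild share differs by 20 points between arms (6 of 30 patients), the observed rates differ by 0.20 × (1 − 0.30) = 0.14, that is 14 points.

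**The case against.** **A fall can still fail the rule.** A reader might infer that mild patients count as improved whatever happens to them. The definition does not support that. If improvement is judged on a post-baseline value, a fall from 250 to 190 meets neither alternative. The inference would hold only if any single value in the 2 weeks, or the baseline value itself, could count, and the protocol does not say so. This part of the objection stands. For the same reason, the model in part 2, which scores all mild patients as improved, is an upper bound on the dilution.

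**Few mild patients may be enrolled.** The Berlin lead-in speaks of moderate to severe impairment, and the weaning rule in section 5.1 applies at a P/F ratio above 150 on a PEEP of 5 cm H2O, which many mild patients would already exceed. Both suggest that the mild share may be small, but neither excludes these patients: mild is listed as a grade under that same lead-in, and no exclusion refers to it. The effect may therefore be modest, and the lower rows of mild share belong in the table.

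**The size rests on assumed inputs.** This is correct. Power is also only 66% with no mild patients at all, so the definition is not the main reason this outcome is underpowered.

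**It is one of seven secondary outcomes.** The secondary objective is worded as exploratory, no power is tied to it, and the intubation comparison is untouched. This stands and limits the severity.

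**Related details are not errors here.** A reader might also infer that a patient who is intubated and then recovers on invasive ventilation would be scored as an NIV success. The outcome is labelled as oxygenation, not NIV success. How intubated patients are scored, and when the blood gas is taken, are details an article commonly leaves to the full protocol or analysis plan. The point does not rest on them.

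**Conclusion.** The point holds in a limited form. Eligibility and the outcome rule, both stated in the protocol, together class every eligible mild patient as at or above the improvement threshold on entry. Those patients then count as improved with no change or after a fall, unless the assessed value is below 200. This is a stated rule that gives a wrong result, not a detail left to another document.

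The size depends on the mild share, which is unknown. Under the assumptions given, the loss runs from 3 points of difference at 10% mild to 15 points at 50% mild (power 66% falling to 57% and 25% respectively). An imbalance of 6 in 30 patients could produce a spurious 14 points.

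It would be wrong to conclude that mild patients can never fail this outcome, or that the trial's main comparison is affected. The rating is should-fix, for one secondary outcome.

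**What to change.** Add a baseline condition to the definition in section 4.4:

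- **Baseline below 200:** improved if the assessed PaO2/FiO2 is at least 200, or has risen by at least 100 from baseline.
- **Baseline 200 or above:** improved only if it has risen by at least 100 from baseline. This is the rise the protocol already states, so no new threshold is needed.

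A simpler alternative is to analyse this outcome only in patients with baseline below 200. A comparison of PaO2/FiO2 adjusted for its baseline value is an optional further choice, not a requirement.

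The cost is the rewording of one outcome. Section 5.1 already has blood gases and PaO2/FiO2 monitored in both groups, and the baseline value is needed for the existing second alternative. The downside is that mild patients face a stricter criterion (an entry value of 201 must reach 301, whereas 199 must reach 200) or leave this one secondary analysis, which reduces its numbers. The change should be dated and made without reference to outcome data by arm.
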